#### Coordinated Action Checklist

Coordinated action is the collaboration of two or more sectors to accomplish an outcome. The Coordinated Action Checklist [47] can be used for the facilitation and evaluation of community health partnerships with different contexts and levels, phase of the program, and participants. It evaluates collaboration for diverse dimensions, such as suitability of partners, task dimension, relation dimension, growth dimension, and visibility dimension. Results will be visualized to give insight into strengths and possible improvements, thereby encouraging feedback and discussion.

#### Timeline method

The Timeline Method [46] sorts out important events and influences inside and outside the network. It gives insight into these events and influences from each participant’s point of view in a certain time frame. This encourages discussion and evaluation to facilitate the collaboration in a positive manner.

#### Levels of collaboration survey

The Levels of Collaboration Survey [48] gives insight into different stages of collaboration with a description of the networking, cooperation, coordination, coalition, and collaboration stages. The stage of collaboration at a given time will be represented by a score on the scale. To measure changes over time, scores will be compared over time.

### SI.2: Conditions at national and local level that facilitate or hinder CSCs

CSCs work in different municipalities and therefore the contexts in which they work will differ. This will lead to differences in the way CSCs operate in forming alliances and to differences in the way local residents’ environmental stream and their physical activity behaviour will be influenced. For that reason, the conditions in national and local policy and the public health capacity of the municipalities will be assessed to identify the context in which each CSC works. Also, CSCs’ experiences with the preconditions for their work will be addressed during the interviews to identify facilitators and barriers.

### Methods and participants

#### Document analysis

To get insight into national and local policy regarding public health and CSCs, a document analysis will be performed every year. National policy and the local policy of each municipality will be analyzed with the use of a checklist based on Rütten et al.’s ADEPT model [49]. ADEPT, which stands for Analysis of Determinants of Policy Impact, aims to explain and influence policy development and policy impact implementation under four headings: goals, obligations, resources, and opportunities. The ADEPT model is useful to elucidate the role of policy processes in health promotion output and outcome. In addition, it is useful to identify necessary conditions in policy for a broker role such as the CSC.

#### Interviews

To assess the local-level conditions in which CSCs are working, policymakers from the nine municipalities will be interviewed. The local public health capacity mapping checklist, based on the frameworks of Meyer et al. [50] and Aluttis et al. [51, 52], the tools of Aluttis et al. [53] and Bagley and Lin [54], and interviews with experts, will be used during the interview to identify the context in which CSCs are working and the contextual changes over a period of time. This will make it possible to compare the capacity of the participating municipalities.

### Tools

#### Local public health capacity mapping checklist

This checklist consists of five dimensions to map the public health capacity of a municipality. These dimensions-policy characteristics, organizational structure, resources, programs and partnerships, and municipal context-are operationalized on the basis of the tools of Allutis et al. [53] and Bagley & Lin [54]. Quantitative operationalizations will be interrogated with a questionnaire prior to the interview wherein the qualitative operationalizations will be addressed. This will give the opportunity to clarify ambiguities in the questionnaire with the policymakers.

### SI.3: Mediated impacts and perceived societal benefits

Physical inactivity is an enormous risk factor for non-communicable diseases, which are currently creating an economic burden due to the increased prevalence of physical inactivity. Because the policy concerning CSCs—to connect primary care, sport, and physical activity and to prevent inactivity—is new and unique, it is necessary to evaluate the perceived benefits for the municipality, its residents, and professionals in the primary care and sports sectors.

### Methods and participants

#### Focus groups

To assess the impact of CSCs and the perceived societal benefits for the municipality, in total 14 focus groups with the CSCs, their alliances, and residents will be held at the end of the project. The aim of these groups is to identify the kind of programs conducted, the perceived results of these programs, and the perceived impact for professionals in the primary care and sports sectors, the neighbourhood, and its residents. The effect arena [55] will be used to structure these focus groups.

### Tools

#### Effect arena

The effect arena [55] structures the dialogue about an intervention’s investments and societal benefits as perceived by stakeholders. This is made possible by the completion of the following steps; problem analysis, determination of zero alternative, determination of project alternatives, identification of costs and effects, quantification and monetization of effects. It gives insight into and the possibility to examine the added value of an intervention; this is the first step towards a societal costs-benefits analysis.

### Data analysis Study I

The interviews and focus groups will be audio-taped and transcribed (intelligent verbatim style). The data analysis will be based on Creswell’s [56] six steps for qualitative data analysis. So, after the transcripts of the interviews and the focus groups are read, they will be coded and analysed using software for qualitative analysis (Atlas.ti, version 7.0). Both top-down and bottom-up coding will be used to analyse the interviews and focus groups. The top-down coding will use with predefined codes based on factors mentioned in the TTI and the HALL framework. The bottom-up coding (free coding) will trace general themes that emerge in the interviews and focus groups. In this way, relevant topics devised in advance of the study design and relevant topics from practice will be fully mapped. The codes will be clustered into themes. These themes will make it possible to interrelate and interpret the data [56].

The data gathered in the cases will be used to describe each case and build explanations on the CSC role in connecting primary care, sport, and physical activity [44]. In addition, we will make use of cross-case synthesis. This cross-case synthesis treats each individual case study as a separate study [44]. Word tables will be used to display the data from the individual cases according to the different frameworks presented in the theoretical framework. These word tables will also be used to analyse whether different groups of cases appear to share some similarities and deserve to be considered instances of the same type of general case [44]. Similar results in this study’s different cases will make it possible to draw general conclusions—for example, factors that hinder or facilitate the connection between primary care, sport, and physical activity.

### Study II

Study II will concentrate on lifestyle programs participants to identify health and physical activity behavior changes. In addition, the study will reveal facilitators for, and barriers to, the implementation of appropriate lifestyle programs.

### SII.1: Lifestyle programs and target groups

Lifestyle interventions aim to improve people’s health on themes such as smoking cessation, reduction of alcohol abuse, health dietary improvement, increased physical activity, or a combination of these themes. This study focuses on physical activity programs, and perhaps also programs in which other themes are also targeted.

Physical activity is defined as bodily movement produced by the contraction of skeletal muscle that increases energy expenditure above the basal level [57]. It can be classified in several ways, such as purpose, intensity, and type. The Dutch Healthy Physical Activity Guideline, which is 30 min of moderate physical activity at least five days a week, takes duration, frequency, and intensity into account [4]. Other elements that are crucial to stay physically active in the long term, revealed in previous studies, are cost, trainer qualifications, environment, and point in time [18, 19, 23, 58]. These elements are relevant to describe in a monitor report, and, additionally, relevant elements described in Wolfenstetter’s conceptual framework [59] will be monitored to create input for a societal costs-benefits analysis.

### Methods and participants

#### Interviews

Interviews will be conducted with the CSC to retrieve information about all the lifestyle programs arranged by, or with the help of, the CSC. During the interview, a table with characteristics of the lifestyle programs will be filled in to get insight into the type of programs and their target groups. These interviews will be held every six months with the 14 CSCs, in conjunction with the interviews of for research question SI.1.

### SII.2: Strategies and preconditions to increase participation, self-management and transferal of primary care patients

As mentioned before, principles such as participation, transferal of patients from primary care to local physical activity facilities, and enhancing self-management are essential but hard to realize in lifestyle programs. This part of the study will focus on these principles to improve the implementability of lifestyle programs.

### Methods and participants

#### Literature study

To gain input for a Delphi study, a literature study will be conducted to get insight into: 1) the different levels of participation and the experiences with community participation in lifestyle interventions, 2) indicators of self-management for individuals with, or at risk of, chronic disease, 3) experiences with the transferal of patients from primary care to local physical activity facilities in the Netherlands, and 4) views and experiences of individuals with, or at risk of, chronic disease on behavior change techniques used to enhance physical activity adherence during, and the maintenance after, a program. In addition, the review of research question SI.1 will be used to get insight into facilitators and barriers for intersectoral collaboration between the primary care and sports sectors.

#### Delphi study

A Delphi study will be carried out to identify strategies to increase participation, self-management, and transferal of patients. The ultimate aim is that this knowledge will contribute to the development of appropriate lifestyle interventions and their implementation. In order to get a comprehensive insight into the barriers and challenges to these different strategies, professionals representing different sectors will be involved in the Delphi study. From each of the following professions, a representative sample of Dutch professionals will be included by random sampling: general practitioner, practitioner nurse, physiotherapist, coordinator of the social neighborhood team, public health policy coordinator, trainers, chairman of a sports club, and CSCs. Additionally, participants of lifestyle programs will be included: 10 potential participants, 10 dropouts, and 10 participants who have completed a lifestyle program.

The first round of the Delphi study will consist of an open-ended questionnaire to discover viewpoints of each profession and participants in relation to physical activity, lifestyle programs, and intersectoral collaboration for the transferal of patients, self-management, and participation. This will reveal opportunities and barriers for the implementation of certain programs, and these will be the input for the statements in round 2. The statements in round 2 will be scored on a 7-point Likert scale by each professional and participant in order to determine which tasks will be recognized as their responsibility to ensure a better implementation of lifestyle programs and the intersectoral collaboration between the health and sports sectors for the transferal of patients. In the third and optional fourth round, there needs to be consensus about the possibilities within each profession and the necessities for each profession. The statements on which consensus is reached will be used to compose a checklist for CSCs to develop and implement lifestyle programs.

### SII.3: Effect in terms of physical activity behavior and maintenance, self-management, quality of life, experienced health, and health gains

The defined outcome of the CSC role is an increased number of residents participating in local sports facilities and being physically active in their own neighbourhood, for which it is necessary that people have the possibility to maintain their physical activities. This goal is proposed because of the increase in non-communicable diseases partly caused by inactivity. It is necessary to know whether the lifestyle interventions arranged by, or with the help of, CSCs influence physical activity behaviors and consequently improve people’s health. Therefore, this part of the study will take the effects of lifestyle interventions into account.

The complex relationship between physical activity, fitness, and health is described by Bouchard and Shephard in the Toronto Model [60]. A basic level of fitness is required for overall health in all individuals, the so-called health-related fitness, defined as ‘an ability to perform daily activities with vigor’ and a lower risk of developing non-communicable diseases. Health-related fitness is divided into five components: morphological, muscular strength and endurance, motor, cardio-respiratory fitness, and metabolic fitness. Physical activity influences health-related fitness directly and consequently has an impact on an individual’s health. The components of health-related fitness are measurable and will form the basis of the fitness test.

However, the concept of health is broader than the measurable components of health-related fitness. Huber et al. [61] introduced the dynamic definition of health as ‘Health as the ability to adapt and to self-manage, in the face of social, physical and emotional challenges’. In 2013, they operationalized the concept into the measurable dimensions of body functions, mental functions and perceptions, spiritual dimension, quality of life, social participation, and daily functioning. This conceptual framework will be used in the current study to decide which topics are relevant to include, in relation to physical activity and health, for a questionnaire to assess the impact on health.

### Methods and participants

In a one-group pretest/post design, lifestyle programs participants will perform a fitness test and fill in a questionnaire to assess their maintenance of physical activity and health gains. This will take place at the start of the lifestyle program (T0), at the end of the lifestyle program (T1), and one year after the start of the lifestyle program (T2).

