**Fig. 3 Fig3:**

Overview of data collection methods and planning of the study. ^1^Care Sport Connectors

Action research provides direct feedback about the results to the CSCs and stakeholders, thus helping them to decide how to continue [40]. This is made possible by the use of tools which facilitate a learning process for CSCs and stakeholders in order to instigate change to improve practice [41]. Process evaluation will be used to monitor and document program implementation and can aid in elucidating the relation between specific program elements and program outcomes [42].

A mixed methodology is suitable for an appropriate multiple case study and action research design [43, 44]. Therefore, data will be collected through interviews, focus groups, document analysis, questionnaires, literature study, and a health-related fitness battery. These methods will be used in multiple rounds over three years to reveal changes over time. The fitness battery will be applied in a one group pre-test/post-test design, with a baseline measurement and two post-tests.

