#### Sample size calculation

The study population of the one-group pretest/ post-test will consists of adults who start a lifestyle program arranged by, or with the help of, the CSC in one of the nine municipalities. Inclusion will be determined by convenience sampling. The sample size calculation is based on alpha = 0.05 and power = 0.80 and assumes additionally:The primary outcome measure is maintenance of physical activity behavior after a lifestyle program, by participating in a local sports or exercise activity. Pilot data from the BeweegKuur revealed that 10–30 %, depending on the context, of the participants continue participating in local sports facilities after the lifestyle program [[name], Personal Communication, November 2012]. The expected value for this study is 40 % because of the introduction of the CSC, although 20 % is set as the criterion for this sample size calculation.Some of the effects will be explainable by differences in support, lifestyle programs, and context in each neighborhood. There are no data available from the BeweegKuur about the intra-class correlation coefficient (ICC). An ICC of 0.15 is assumed, based on research into common values and similar interventions [62–65].

The required number of participants is 414, which will lead to 258 independent observations due to a design effect of 1.6. On the assumption of a drop-out rate of 10 % during the lifestyle program [66], 10 % at T1, and 20 % at T2 [67], a baseline sample of 640 participants is required.

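### T2 is timed from programme start but the primary outcome runs from programme end, so post-programme follow-up varies with programme length

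*Protocol article*

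**What the plan says.** The relevant statements are in Study II of the protocol article.

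- **Visits** (SII.3, Methods and participants). For baseline: "This will take place at the start of the lifestyle program (T0". The two later measurements come "at the end of the lifestyle program (T1), and one year after the start of the lifestyle program (T2". T0 and T2 are thus anchored to the start of the programme and T1 to its end. The Study design section likewise describes a one-group design "with a baseline measurement and two post-tests".
- **Primary outcome** (Sample size calculation). "The primary outcome measure is maintenance of physical activity behavior after a lifestyle program, by participating in a local sports or exercise activity". It is defined relative to the end of the programme. No visit, time point or minimum interval after the end is attached to it.
- **Who is included** (Sample size calculation). The sample is "adults who start a lifestyle program arranged by, or with the help of, the CSC in one of the nine municipalities", recruited by convenience. No minimum or maximum programme length is given.
- **Expected variation** (Sample size calculation). "Some of the effects will be explainable by differences in support, lifestyle programs, and context in each neighborhood". Programmes are therefore expected to differ from place to place.
- **Use of the result** (Discussion, Strengths and limitations). Individual results are to be linked to findings about the intervention, the environment and policy, to explain why behaviour did or did not change.

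**The concern.** Maintenance after a programme means little without a statement of how long after. Here that time is whatever remains of the first year once the programme is over. A participant from a short programme must keep going for most of a year to count as maintaining at T2. A participant from a longer programme needs only a few months. If people stop gradually once a programme ends, the longer programme shows the higher rate even when behaviour is the same.

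The explanatory aim is what is at stake. Programme length is a feature of the intervention and may go with a particular connector or municipality. A difference produced by the visit schedule could be read as an effect of programme or context. The overall maintenance proportion would also be an average over an unstated mix of follow-up times.

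**Working it through.** **Step 1: which visit carries the primary outcome.** The article does not name one, but its sample size points to T2. Inputs from Sample size calculation: 414 participants required, with losses of 10 % during the programme, 10 % at T1 and 20 % at T2.

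414 / (0.9 × 0.9 × 0.8) = 414 / 0.648 = 638.9, or 639 rounded up, against the stated 640. In reverse, 640 × 0.648 = 414.7.

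The stated figure reproduces. The 414 are therefore participants still measured at T2. A separate 20 % loss at T2 also shows that the plan presumes a real interval after T1.

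**Step 2: length of the post-programme window.** Let L be programme length in months. T1 falls at month L and T2 at month 12, so

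window = T2 − T1 = 12 − L.

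The article gives no value of L; those below are assumptions.

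| L (months) | Window (months) |
|---|---|
| 3 | 9 |
| 6 | 6 |
| 9 | 3 |

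Each extra month of programme removes one month of follow-up. At L = 12 the window is 0, and above 12 T2 would precede T1.

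**Step 3: what unequal windows could do.** The article gives no rate of decline after a programme, so this is an illustration over a range. Assume 40 % are active at programme end (the article's expected value, used here as a starting point) and a constant share h of them stops each month. Then rate at T2 = 0.40 × (1 − h)^(12 − L).

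| h per month | L = 3 | L = 6 | L = 9 | Spread, L = 3 to 9 |
|---|---|---|---|---|
| 3 % | 30.4 % | 33.3 % | 36.5 % | 6.1 points |
| 5 % | 25.2 % | 29.4 % | 34.3 % | 9.1 points |
| 10 % | 15.5 % | 21.3 % | 29.2 % | 13.7 points |

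Behaviour is identical within each row; only the visit timing differs. For scale, the criterion of 20 % and the expected value of 40 % in Sample size calculation are 20 points apart, so the spread is 6.1/20 = 0.3 to 13.7/20 = 0.7 of that gap. With h = 0 there is no spread.

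**Step 4: effect on the sample size.** The figures 258, 414 and 640 contain no follow-up time. They do not change unless participants are removed from the analysis.

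**The case against.** The strongest defence is that one year from baseline is a sensible anchor. T2 also serves the change in fitness and health since T0, for which it gives equal elapsed time and the same season. That stands, and it is a reason not to move T2. It does not help an outcome defined from programme end.

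A second defence is that programme length and covariates belong in a full protocol or analysis plan. That is fair as to the missing lengths. But the T2 anchor and the outcome definition are both stated here, and they do not fit each other. Part of the remedy is also already within reach: T1 takes place at programme end, so its date yields the interval.

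Three stronger readings are tempting, and the article does not support them.

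- *Some participants have no follow-up, so their primary outcome cannot be observed.* This needs a programme of 12 months or more. None is described, and the separate loss budgeted at T2 suggests that a gap was expected. It is a possibility only.
- *Every programme in the inventory enters the primary analysis.* The interviews in SII.1 collect "information about all the lifestyle programs arranged by, or with the help of, the CSC", but that is an inventory. The SII.3 participants are a convenience sample.
- *The comparison with the BeweegKuur pilot is biased.* The 10–30 % is given without time since programme end, so no bias can be shown, and re-anchoring T2 would not by itself align the two.

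Strengths and limitations also rules out estimating a general effect of the connectors. The concern is therefore with explaining differences and interpreting the proportion, not with a claim of overall effectiveness.

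**Conclusion.** The point holds as a mismatch between two stated anchors. Post-programme follow-up is 12 months minus programme length; it follows directly from the visit schedule and varies as soon as programmes differ in length. The article expects programmes to differ, though it does not say specifically that their lengths do.

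The size of the effect on the maintenance rate is not known. Under the assumed lengths of 3 to 9 months and monthly losses of 3 to 10 %, it is 6 to 14 percentage points between programmes with the same underlying behaviour. That rests on a decline after programme end, which the article does not quantify. The unequal window does not rest on it.

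The change is worth making before analysis. The fitness and health outcomes, as changes since T0, are unaffected.

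**What to change.** 1. Keep T2 at one year after programme start for the fitness and health outcomes.
2. Record each participant's programme end (T1) date and derive the T1–T2 interval.
3. Include that interval in the primary maintenance analysis, and report the maintenance proportion by interval or standardised to one stated post-programme interval.
4. Do not count as maintaining anyone whose programme is still running at T2; report how many there are.
5. Where the data-collection period allows, add a short questionnaire at a fixed interval after T1 and make it the primary maintenance measure.

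Item 5 has a statistical reason. With T2 fixed, the interval is exactly 12 minus programme length, so a model can describe maintenance by interval but cannot separate time since the end from an effect of programme length itself. A measurement at a fixed time after T1 can.

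The cost of items 1 to 4 is slightly more analysis work and some loss of precision if lengths vary widely. Item 5 adds a contact and may not fit late entrants to long programmes, since the Study design section closes the study at the end of 2016. Excluding participants with short intervals is not advised: programme lengths are unknown, and the loss could erode the required 414.
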